## Abstract

**Background:** Cancer cachexia and exacerbated fatigue represent two hallmarks in cancer patients, negatively impacting their exercise tolerance and ultimately their quality of life. However, the characterization of patients' physical status and exercise tolerance and, most importantly, their evolution throughout cancer treatment may represent the first step in efficiently counteracting their development with prescribed and tailored exercise training. In this context, the aim of the PROTECT-01 study will be to investigate the evolution of physical status, from diagnosis to the end of first-line treatment, of patients with one of the three most common cancers (i.e., lung, breast, and colorectal).

**Methods:** The PROTECT-01 cohort study will include 300 patients equally divided between lung, breast and colorectal cancer. Patients will perform a series of assessments at three visits throughout the treatment: (1) between the date of diagnosis and the start of treatment, (2) 8 weeks after the start of treatment, and (3) after the completion of first-line treatment or at the 6-months mark, whichever occurs first. For each of the three visits, subjective and objective fatigue, maximal voluntary force, body composition, cachexia, physical activity level, quality of life, respiratory function, overall physical performance, and exercise tolerance will be assessed.

**Discussion:** The present study is aimed at identifying the nature and severity of maladaptation related to exercise intolerance in the three most common cancers. Therefore, our results should contribute to the delineation of the needs of each group of patients and to the determination of the most valuable exercise interventions in order to counteract these maladaptations. This descriptive and comprehensive approach is a prerequisite in order to elaborate, through future interventional research projects, tailored exercise strategies to counteract specific symptoms that are potentially cancer type-dependent and, *in fine*, to improve the health and quality of life of cancer patients. Moreover, our concomitant focus on fatigue and cachexia will provide insightful information about two factors that may have substantial interaction but require further investigation.

**Trial registration:** This prospective study has been registered at ClinicalTrials.gov (NCT03956641), May, 2019.

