## Materials and Methods

### Study Population

As they represent ~30% of all newly diagnosed cancers (51), this cohort study will focus on three different cancer types: breast, lung, and colorectal. The detailed inclusion and exclusion criteria are summarized in Table 1.

**Table 1 T1:** Inclusion and exclusion criteria.

**Inclusion criteria**	**Exclusion criteria**
• First-line cancer treatment	• Psychiatric, musculoskeletal, or neurological disorders
• Breast cancer, Stage II or III, treated by taxane-based CT	• Pregnant or nursing women
• Colorectal cancer, stage IV, treated by CT, RT, IT, or TT	
• Non-small cell lung cancer, stage III or IV, treated by CT, RT, IT, or TT	
• Age ≥18 years	
• Performance status WHO 0–2	
• Life expectancy >6 months	
• Ability to speak, understand and read French	
• No contraindication to physical assessments	
• Affiliate to social security system	
• Give written inform consent	

*CT, chemotherapy; IT, immunotherapy; RT, radiation therapy; TT, targeted therapy; WHO, World Health Organization performance status*.

Patients newly diagnosed with cancer by an oncologist and satisfying inclusion and exclusion criteria described in Table 1 will be informed of the study protocol. If interested, the patient will contact one of the study coordinators for full information about the study as well as to discuss any questions pertaining to it. Once the patient has provided the written consent form to participate in this study, the visits will be scheduled.

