### Sample Size

An *a priori* sample size estimation was performed using the following sample size calculation formula (68):

$$\begin{array}{l} Sample\;size\;=\;\frac{{Z_{-a/2}}^{2}SD^{2}}{d^{2}} \end{array}$$

Where: *Z*_−*a*/2_ is a standard normal variate (at 5% type 1 error i.e., *P* < 0.05, it is 1.96); *SD* is the standard deviation of the main variable based on previous study; and *d* is the absolute error or precision based on previous study.

The primary outcome of this study is to investigate the evolution of exercise tolerance using the 6-MWT distance. According to Granger et al. (69), a 9.5% decline in the walking distance (i.e., exercise performance) during the 6-MWT test is sufficient to show a clinical decrease in exercise tolerance. Thus, based on the evolution of 6-MWT distances between the first and the second visit in our study, the hypothesis was that cancer patients will reduce, by at least 9.5%, their 6-MWT performance, and thus exhibit signs of exercise intolerance. We also determined the expected baseline 6-MWT results (659 ± 62 m) from the results observed in a healthy subjects group aged 55–75 years old (70), and a 7-m precision was calculated according to a test-retest reliability performed by Demers et al. (67). Using an α level of 0.05 and a power (1-β) of 0.95, the total sample size was calculated as follows:

$$\begin{array}{l} Sample\;size=\frac{1.96^{2}{\left(62\right)}^{2}}{7^{2}}=301 \end{array}$$

Our sample (*n* = 301) will be equally divided into our three groups of interest: 100 lung cancer patients, 100 breast cancer patients, and 100 colorectal cancer patients.

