### Statistical Analysis

Normality and variance homogeneity will be investigated on all collected data using the Shapiro-Wilk test and the Levene test, respectively. Appropriate parametric or non-parametric analyses will then be performed. Statistical significance will be set at *P* < 0.05. All values will be expressed as mean ± standard deviation or median ± range.

A multivariate analysis of variance (MANOVA) will be used on our primary outcome (i.e., exercise tolerance) and secondary outcomes (i.e., quality of life, fatigue, physical activity level, strength, fatigability, body composition, cachexia, physical performance, and respiratory function) to protect against Type I errors arising from multiple comparisons. A two-way mixed-design ANOVA will be used (group [lung cancer – colorectal cancer – breast cancer] × time [first visit – second visit – third visit]). Finally, if a significant difference is found, a multiple-comparison analysis will be performed using an appropriate *post-hoc* test.

Finally, interaction between specific variables will be tested with Pearson's correlation coefficients (*r*^2^). For example, we plan to test the possible correlation between subjective and objective fatigue, or between exercise tolerance/quality of life and body composition.

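### The calculated 301 is taken directly as the enrolled sample (in fact 300), with no allowance for loss before Visits 2 and 3, so the stated 7 m precision holds essentially only with complete data

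*Protocol article*

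**What the plan says.** The Sample Size section uses a one-mean precision formula, Z² × SD² / d². The SD comes from the "expected baseline 6-MWT results (659 ± 62 m) from the results observed in a healthy subjects group aged 55–75 years old". For d, "a 7-m precision was calculated according to a test-retest reliability". The result is 301. The article calls this its sample, which "will be equally divided into our three groups of interest: 100 lung cancer patients, 100 breast cancer patients, and 100 colorectal cancer patients". The Abstract gives the total as 300: the study "will include 300 patients equally divided between lung, breast and colorectal cancer".

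The same section names the evolution of 6-minute walk distance as the primary outcome and hypothesises a fall of at least 9.5% between the first and second visits. Under Statistical Analysis, "A two-way mixed-design ANOVA will be used", with three cancer groups and three visits. Study Design places Visit 3 just after first-line treatment ends or at 6 months, whichever is earlier.

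Table 1 admits stage II or III breast cancer, stage III or IV non-small cell lung cancer and, for the third group, "Colorectal cancer, stage IV, treated by CT, RT, IT, or TT". It allows WHO performance status up to 2 and requires a life expectancy above 6 months. The article gives no loss rate, no inflation step and no expected number of evaluable patients.

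**The concern.** A precision formula returns the number of patients who must contribute data. Here that number is also the number to be included, so the calculation implies that every patient is measured whenever the analysis needs them. For the Visit 1 to Visit 2 hypothesis that means paired distances from everyone. For the mixed-design ANOVA, which in its standard form drops a patient with a missing visit, it means three distances from everyone.

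Complete follow-up is a strong assumption in this cohort. The lung and colorectal groups, 200 of 300 patients, are stage III or IV by entry criterion, and some breast patients will be stage III. The article itself links walking distance to mortality (Exercise Tolerance) and describes cachexia as more prevalent in lung and colorectal than in breast cancer (Expected Impact and Perspectives). Loss could therefore differ between the groups and be related to the outcome, although the article gives no figures for either.

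At stake is whether the size and precision that readers will credit to the study are those of the data it will analyse, and whether the equal division into three groups will survive into the analysis.

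**Working it through.** **Inputs (all from Sample Size unless noted).** Z = 1.96; SD = 62 m; d = 7 m; expected baseline mean 659 m; hypothesised decline 9.5%; enrolled 3 × 100 = 300 (also Abstract). Assumed here because the documents give no values: losses of 10%, 20% and 30%; the correlation ρ between visits; equal SDs at the visits.

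**1. Reproducing the stated size.**
1.96² × 62² / 7² = 3.8416 × 3844 / 49 = 301.37.
This is the stated 301 (302 if rounded up). It is the raw result, with no division by (1 − loss). The section also mentions a power of 0.95, but the formula has no power term, so the result is checked here as a precision calculation only.

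**2. Precision at the enrolled number.** Half-width = 1.96 × 62 / √n = 121.52 / √n.
- n = 301: 7.00 m
- n = 300: 7.02 m

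The 301/300 mismatch costs about 0.01 m.

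**3. Precision after loss, same formula and SD.**

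| Assumed loss | Evaluable of 300 | Half-width |
|---|---|---|
| 0% | 300 | 7.02 m |
| 10% | 270 | 7.40 m |
| 20% | 240 | 7.84 m |
| 30% | 210 | 8.39 m |

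For scale, keeping 301 evaluable would mean enrolling 301 / 0.9 = 335, 301 / 0.8 = 377 or 301 / 0.7 = 430 patients.

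**4. What these half-widths describe.** The 62 m is a between-subject SD of distance at one time. The primary outcome is a change, whose SD under equal visit SDs is 62 × √(2(1 − ρ)).
- ρ = 0.5: SD of change = 62 m, so the table in step 3 applies unchanged.
- ρ = 0.85 (the reproducibility coefficient quoted under Exercise Tolerance, used only as an illustration): SD of change = 62 × √0.30 = 34.0 m. Even with 180 evaluable (40% loss) the half-width is 1.96 × 34.0 / √180 = 5.0 m.
- Correlation at which the change still has a 7 m half-width: about 0.60 with 240 evaluable and about 0.65 with 210.
- ρ = 0: SD of change = 87.7 m, and the half-widths are √2 times those in the table.

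**5. Detecting the hypothesised decline.** 9.5% × 659 = 62.6 m. With an SD of change of 62 m and only 60 patients in a group, the standard error is 62 / √60 = 8.0 m. The decline is then 7.8 standard errors, and power against no change is close to 100%. With ρ = 0 the standard error is 87.7 / √60 = 11.3 m and the decline is still 5.5 standard errors.

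**The case against.** Four objections deserve an answer.

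*The 301/300 difference is rounding.* This stands. A reader might infer that the 7 m target is missed even with no loss, but 7.02 m against 7.00 m comes only from dividing 301 into three equal groups.

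*It is not shown that 7 m is out of reach for the primary outcome.* This also stands. The 62 m is a baseline SD from healthy people. Baseline precision is untouched by later loss, and precision for the change depends on an SD that the article does not give. With a high enough correlation between visits, a 7 m half-width for the change survives substantial loss (step 4). The documents therefore do not support saying that 7 m cannot be met. They support saying that the protocol's own calculation delivers it essentially only with complete data.

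*Attrition is inferred, and nothing is threatened.* In part this stands. No loss rate is documented, Visit 2 is only 8 weeks into treatment, and entry requires a life expectancy above 6 months. A reader might infer that the study is underpowered; step 5 shows that it is not for the hypothesised decline. But three-visit analyses extend to 6 months, and zero loss is itself an assumption, made without support.

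*A condensed article may leave this to a fuller document.* Missing-data handling may indeed be left there, and its absence is not criticised here; the article does not say that incomplete patients are excluded. The sample size is different. The article shows the calculation from formula to allocation and equates its result with the sample. An allowance for loss elsewhere would make enrolment exceed the calculated number, which contradicts both the Sample Size section and the Abstract.

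**Conclusion.** The point holds in a limited form. The number required by the calculation is also the number enrolled, with no allowance for loss, in a cohort that is at least two thirds stage III-IV and an analysis that relies on repeated visits. On the protocol's own formula and SD, the precision goes from 7.02 m with complete data to about 7.4, 7.8 and 8.4 m at assumed losses of 10%, 20% and 30%, an erosion of about 0.4 to 1.4 m.

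Those figures rest on assumed loss rates and a healthy-subject baseline SD. They describe a mean distance, and carry over to the Visit 1 to Visit 2 change only at a between-visit correlation of about 0.5. The defect is in the stated size and precision; it does not put the study's ability to show the hypothesised decline in doubt. It should be corrected because the correction is cheap and the present text claims a precision that its own calculation does not support once patients are lost.

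**What to change.** Keep 300 enrolled; no additional patients are needed. In Sample Size, give 300 as the sample, in line with the Abstract, and note that 301 was rounded to three equal groups. State the number expected to be evaluable at Visit 2 and at Visit 3, overall and for each cancer. Replace the single 7 m figure with the precision at those numbers, naming the loss rate and the SD assumed.

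The text should say whether that precision refers to a mean distance or to the Visit 1 to Visit 2 change. If it is the change, give the assumed SD of change or between-visit correlation. The 7.4 to 8.4 m range above should not be printed as the precision of the change without that assumption beside it.

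The cost is the rewording of one paragraph and a stated precision that becomes slightly less favourable. No procedure, visit or analysis changes.

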### Statistical Analysis

Normality and variance homogeneity will be investigated on all collected data using the Shapiro-Wilk test and the Levene test, respectively. Appropriate parametric or non-parametric analyses will then be performed. Statistical significance will be set at *P* < 0.05. All values will be expressed as mean ± standard deviation or median ± range.

A multivariate analysis of variance (MANOVA) will be used on our primary outcome (i.e., exercise tolerance) and secondary outcomes (i.e., quality of life, fatigue, physical activity level, strength, fatigability, body composition, cachexia, physical performance, and respiratory function) to protect against Type I errors arising from multiple comparisons. A two-way mixed-design ANOVA will be used (group [lung cancer – colorectal cancer – breast cancer] × time [first visit – second visit – third visit]). Finally, if a significant difference is found, a multiple-comparison analysis will be performed using an appropriate *post-hoc* test.

Finally, interaction between specific variables will be tested with Pearson's correlation coefficients (*r*^2^). For example, we plan to test the possible correlation between subjective and objective fatigue, or between exercise tolerance/quality of life and body composition.

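### The method for the primary 6-MWT depends on Shapiro-Wilk and Levene pre-tests with no trigger and no named fallback, yet the same section says a mixed ANOVA will be used

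*Protocol article*

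**What the plan says.** All of this stands in the Statistical Analysis section of the protocol article, except the definition of the primary outcome.

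- Pre-tests: "Normality and variance homogeneity will be investigated on all collected data using the Shapiro-Wilk test and the Levene test, respectively".
- Consequence: "Appropriate parametric or non-parametric analyses will then be performed". The sentence covers every outcome and makes no exception for the primary one.
- Level: "Statistical significance will be set at *P* < 0.05".
- Next paragraph, without any condition: "A two-way mixed-design ANOVA will be used", with three cancer groups and three visits, after a MANOVA across primary and secondary outcomes.
- Follow-up: "a multiple-comparison analysis will be performed using an appropriate *post-hoc* test".
- Primary outcome, in the Sample Size section: "The primary outcome of this study is to investigate the evolution of exercise tolerance using the 6-MWT distance".

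Every method named after the pre-tests is parametric (MANOVA, mixed ANOVA, Pearson correlation). No non-parametric method is named.

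**The concern.** The two paragraphs do not fit together. The first makes the method conditional on the data, and the second names one method outright. Someone analysing the 6-MWT could defend either route after seeing the pre-test results.

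The pre-tests are also a poor basis for the choice at this sample size. With 100 patients per group, Shapiro-Wilk detects departures that do no harm to an ANOVA. With many group-by-visit cells, some test will often reject by chance.

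What is at stake is the comparison of evolution between lung, breast and colorectal cancer, which the Discussion (Rationale and Novelty) presents as a main purpose. If the switch leads to rank tests visit by visit, or within each cancer separately, that comparison is no longer tested.

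**Working it through.** **Inputs from the document.** SD 62 m, baseline mean 659 m, precision 7 m, expected decline 9.5%, 100 patients per group (Sample Size); α = 0.05, Shapiro-Wilk, Levene, 3 groups × 3 visits (Statistical Analysis).

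**Assumed, because the document gives no value.** Between-visit correlation 0.7 to 0.85; the same SD at all visits; skewness 0.5 to 0.71; group means 75 m apart where groups differ in step 4; and a trigger of any rejection among 9 group-by-visit Shapiro-Wilk tests and 3 per-visit Levene tests.

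**1. The plan's own figure.** n = 1.96² × 62² / 7² = 301.37, which reproduces the stated 301. This point does not dispute it.

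**2. Normal data.** If the 12 tests were independent, the chance of at least one rejection would be 1 − 0.95¹² = 0.46. Visits are correlated, so simulation is the better guide. With correlation 0.8 and 3,000 runs, at least one Shapiro-Wilk test rejected in 33% of datasets, at least one Levene test in 11%, and either in 41%. With correlation 0.85, two further simulations gave 39% and 40%. The uncorrected interaction F-test rejected in 5.4% of the correlation-0.8 runs.

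**3. Mildly skewed data.** The switch fired in 96% of datasets at skewness 0.5 and in 99% at about 0.71. These rates depend somewhat on how the skewness is generated, so they are best read as more than nine in ten. At 0.71 the mixed ANOVA kept its level: time 4.9%, interaction 5.0%.

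**4. If the tests are run on raw values pooled over groups and visits.** Data normal within groups, with equal means, were rejected in 23% of runs, because repeated values from one patient are treated as independent. With group means 75 m apart this rose to 69%. On this reading a real difference between cancers can itself trigger the switch.

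**5. What the switch costs depends on the fallback.**

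*Kruskal-Wallis at each visit.* This compares levels, not evolution. With 100 per group the standard error of a difference between two group means is 62 × √(2/100) = 8.77 m. A constant 75 m gap is therefore 75 / 8.77 = 8.6 standard errors, and is rejected almost surely even if all groups evolve alike. A simulation with assumed baseline differences and no interaction rejected at visit 3 in 99.9% of runs. Power is lost too. The SD of a change score is 62 × √(2(1 − r)), which is 34.0 m at r = 0.85. The variance ratio of level to change is 1 / (2 × 0.15) = 3.3. For one assumed difference in evolution, power was 39% for Kruskal-Wallis at visit 3, 83% for the mixed ANOVA and 89% for Kruskal-Wallis on change.

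*Friedman within each cancer.* This gives three separate tests of time and no test between groups.

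*Kruskal-Wallis on change from visit 1.* The whole two-stage rule was simulated with correlation 0.7, 3,000 runs and an assumed 20 m group difference in change:

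| Data | Type I error, two-stage | Power, two-stage | Power, ANOVA on change alone |
|---|---|---|---|
| Normal | 5.7% | 84.9% | 85.5% |
| Skewness 0.5 | 5.1% | 89.0% | 86.5% |
| Skewness 0.7 | 4.8% | 91.1% | 87.2% |

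On normal data ANOVA alone also had a type I error of 5.7%. With this fallback the switch is nearly harmless.

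**6. The decline named in Sample Size.** 9.5% of 659 m is 62.6 m. At r = 0.7 the SD of change is 62 × √0.6 = 48.0 m, so the standard error in one group of 100 is 4.8 m and the decline is about 13 standard errors. Any sensible paired test would show it.

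**The case against.** The strongest reply is that the switch has not been shown to do damage. With a rank test on change scores as fallback, error rate and power are about as good as with ANOVA alone, and slightly better on skewed data. The hypothesis in Sample Size is a within-patient decline from visit 1 to visit 2, which ordinary paired rank tests handle. The study calls itself descriptive, and a condensed article may leave the named model to a statistical analysis plan that is not shown. All of this stands, and it limits the severity. It does not remove the point, because the article states a rule that a later plan would inherit and then contradicts it in the next paragraph.

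A reader might infer more than the document supports:

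- *That a non-parametric fallback cannot test group × time.* It can, by Kruskal-Wallis on change or by rank-based factorial methods. The fallback is simply unnamed.
- *That the ANOVA will be run without a sphericity correction and so exceed 5%.* The article is silent, and such a correction is detail that an article commonly leaves out. Under various assumed covariances the uncorrected interaction test ran at 6.2% to 8.3%, but the document gives no visit correlations or later-visit SDs. This is not a separate finding.
- *That 46% of normal datasets would be switched.* This needs independent tests as well as the any-rejection trigger. Correlated visits give about 40%, and the trigger itself is assumed.
- *That the tests are certainly on raw values.* That is the natural reading, but the wording does not exclude residuals.

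**Conclusion.** The point holds in a limited form. The text lets pre-tests decide the method for the primary 6-MWT, also names the mixed ANOVA unconditionally, and does not say which prevails or what the alternative is. Under an any-rejection trigger, about 40% of normal datasets and more than 90% of mildly skewed ones would leave an ANOVA that works at this sample size. These rates rest on the assumed trigger, correlations and skewness.

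The consequence runs from negligible (rank test on change) to loss of the between-cancer comparison (per-visit or within-group rank tests). The document leaves open which applies. The expected overall decline in 6-MWT distance is not at risk. Severity is low to moderate.

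**What to change.** - Delete the pre-test switch for the 6-MWT and state one primary model in advance. This could be a group × time repeated-measures model with unstructured within-patient covariance, or the mixed ANOVA with Greenhouse-Geisser correction always applied.
- Check residuals graphically and do not let the check change the primary model.
- Name one rank-based analysis, for example Kruskal-Wallis on change from visit 1, as sensitivity only.
- For secondary outcomes expected to be clearly skewed, such as the GPAQ score, name the transformation or rank-based model beforehand.

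The cost is a change of wording and a little extra analysis. It needs no new patients, visits or measurements, and the sample size is unaffected.

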### Body Composition and Cachexia

Body mass and composition analyses will be performed using a bioelectrical impedance meter (SECA mBCA 515, SECA, Hamburg, Germany), validated in comparison to different robust methods assessing body composition, such as air-displacement plethysmography, dual-energy X-ray absorptiometry, and deuterium dilution (55). The bioelectrical impedance meter is also regularly used in studies investigating body composition in cancer patients (56–59). We will quantify body mass, fat free mass, fat mass, skeletal muscle mass, visceral fat, and body water repartition. Patient height will be measured to calculate body mass index (BMI, body mass/height^2^).

In accordance with Fearon et al. (4), cachexia will be diagnosed using fat-free mass index cut-off (i.e., <14.6 kg/m^2^ for men and <11.4 kg/m^2^ for women) assessed by a bioelectrical impedance meter (4). Furthermore, the severity of the cancer-related body mass loss (i.e., cachexia) will be investigated using the Martin score (28) at the second and third visit. Martin score is a robust grading system incorporating the independent prognostic significance of both BMI and percentage of body mass loss based on a correlation matrix from a cohort of more than 8,000 cancer patients (28). A severity stage of body mass loss between 0 and 4 is attributed to each patient according to their BMI at cancer diagnosis (28), with stage 0 being the lowest severity stage of cachexia, and stage 4, the highest. Importantly, each score is associated with a specific cumulative survival curve: the lower the score, the greater the survival probability (28).

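### Cachexia is defined as a yes/no diagnosis and a 0–4 stage scored only at Visits 2 and 3, yet it is assigned to the MANOVA and a three-visit mixed ANOVA

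*Protocol article*

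**What the plan says.** **Definition (protocol article, Body Composition and Cachexia).** Two measures are given. The first is a diagnosis: "cachexia will be diagnosed using fat-free mass index cut-off", with separate limits for men and women. The second is severity: "A severity stage of body mass loss between 0 and 4 is attributed to each patient", obtained "using the Martin score (28) at the second and third visit". Table 2 agrees on timing, since its cachexia row is blank at Visit 1 and marked at Visits 2 and 3.

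**Analysis (Statistical Analysis).** Cachexia is named among the secondary outcomes entered in the MANOVA: "quality of life, fatigue, physical activity level, strength, fatigability, body composition, cachexia, physical performance, and respiratory function". The model follows: "A two-way mixed-design ANOVA will be used (group [lung cancer – colorectal cancer – breast cancer] × time [first visit – second visit – third visit". Before that, "Normality and variance homogeneity will be investigated on all collected data using the Shapiro-Wilk test and the Levene test, respectively", and "Appropriate parametric or non-parametric analyses will then be performed". On reporting: "All values will be expressed as mean ± standard deviation or median ± range". A post-hoc comparison follows a significant result, but the test is not named. No categorical or ordinal model appears, and neither do counts with percentages.

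**The concern.** The article makes a positive choice of method for cachexia, and that choice does not fit either measure it defines.

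- **Stage.** A factor with three visits needs three measurements. The stage has two. It is also ordinal, and a mean ± SD treats its five levels as equally spaced.
- **Diagnosis.** The variance of a 0/1 outcome is fixed by its prevalence. When prevalence differs between cancers, the variances differ too, whereas the mixed ANOVA has one error term for all groups.
- **Summaries.** The median and range of a 0/1 variable say almost nothing, and its SD only restates the prevalence.

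Cachexia is one of the two main themes of the study. Under Expected Impact and Perspectives, differences in its prevalence between cancers are used to suggest different exercise for different patients. Within-cancer change in cachexia, and its comparison between cancers, should therefore carry correct uncertainty.

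**Working it through.** **1. Plan's own figure.** The article gives no figure for the cachexia analysis. The group size comes from the sample size section: 1.96² × 62² / 7² = 301.4, stated as 301 and split into 100 per cancer. This reproduces.

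**2. Visits.** The stage exists at 2 visits and the time factor has 3 levels. The Visit 1 cells are empty for the stage in all three groups, so neither the three-level time effect nor the interaction can be estimated. This needs no assumption. The diagnosis could be computed at Visit 1, because body composition is measured at every visit, but Table 2 does not schedule cachexia there.

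**3. Size of the pooled-error effect for the diagnosis.** Inputs:
- 100 patients per group and a 5% significance level (from the article).
- Prevalence about 50%, higher in lung or colorectal than in breast (Expected Impact and Perspectives). It is taken here as 50% in both lung and colorectal.
- Breast prevalence is not given. It is assumed at 10–20%, with 5% and 40% as outer values.
- The same within-person correlation in every group (assumed).

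With v = p(1−p), the ratio of pooled to true standard error for a within-group change is r = √(mean of v over groups / v in that group). The type I error is 2 × [1 − Φ(1.96 r)].

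Breast at 10%: v = 0.25, 0.25, 0.09, with mean 0.59 / 3 = 0.197.
- Lung and colorectal: r = √(0.197 / 0.25) = 0.887, error 8.2%.
- Breast: r = √(0.197 / 0.09) = 1.478, error 0.4%.

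Breast at 20%: v = 0.25, 0.25, 0.16, with mean 0.66 / 3 = 0.22.
- Lung and colorectal: r = 0.938, error 6.6%.
- Breast: r = 1.173, error 2.2%.

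| Breast prevalence (assumed) | Lung, colorectal | Breast |
|---|---|---|
| 5% | 9.4% | <0.1% |
| 10% | 8.2% | 0.4% |
| 20% | 6.6% | 2.2% |
| 40% | 5.2% | 4.7% |

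**4. Simulation, no change in any group, 100 per group, two visits.** Two assumed ways of linking the visits were used: a latent normal variable with correlation 0.7, and 25% of cases reverting with equal numbers of new cases.

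| Breast prevalence | Ungated, lung and colorectal | Ungated, breast | Lung and colorectal after a significant time or interaction test |
|---|---|---|---|
| 10% | 7.7–9.6% | 0.0–0.6% | 3.9–5.0% |
| 20% | 6.1–8.0% | 0.6–2.6% | 3.1–4.2% |

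In these runs the omnibus time test rejected 4.9–5.1% and the interaction test 5.1–5.9%. With each group's own paired standard error, the within-group error was 5.1–5.5% in lung and colorectal and 4.1–5.2% in breast.

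**5. Stage over Visits 2–3, assumed distributions.** When groups differ, the pooled contrast rejects 6.0–8.5% in the groups with higher stages and 2.2–3.4% in those with lower stages.

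**The case against.** **Pooled error is not stated.** This is correct. The post-hoc test is left open, so the error rates above are conditional on a pooled-error contrast.

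**The normality and Levene checks lead to a non-parametric route.** A 0/1 variable will fail Shapiro-Wilk, and a non-parametric analysis could be read to include McNemar, Cochran's Q or Fisher tests. A journal article may also leave the choice to the analysis plan. That softens the point. But the article does name a model for cachexia, and none of those tests gives a group × visit model for a binary or ordinal outcome. The missing Visit 1 stage is untouched by any distributional check.

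**The significance gate protects the contrasts.** It does when nothing changes in any group, where the error falls to 5% or below. If one cancer truly changes, the gate opens more often and gives less protection to the others.

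**Stronger readings a reader might infer, which the article does not support:**
- *False positives arise wherever cachexia is common.* Inflation follows p(1−p). At 80%, 80% and 50%, the error is 3.3% in the two commoner groups and 8.8% in the third.
- *The error rate is 15% or more.* That needs one group far from the others. At 35%, 15% and 3% with 25% reverting, the lung contrast rejects about 17% ungated and about 8% gated. The article names two higher-prevalence cancers, not one.
- *A significant interaction under a common odds ratio is a false positive.* An odds ratio of 2 from 3%, 15% and 30% gives 5.8%, 26.1% and 46.2%, which are rises of 2.8, 11.1 and 16.2 points. On the absolute scale that interaction is real, so this is a choice of scale.

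**Limited reach.** Cachexia is a secondary outcome in a descriptive cohort, and the primary outcome, walking distance, is not affected.

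**Conclusion.** The point holds as a mismatch between the outcome definition and the stated method. The firmest part needs no assumption: the 0–4 stage has no Visit 1 value, so the three-visit ANOVA cannot be fitted to it. The diagnosis is binary and is assigned a model and summaries meant for continuous data.

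The numerical consequence is moderate and conditional. If post-hoc contrasts use pooled error, with lung and colorectal near 50% and breast assumed at 10–20%, the ungated within-group type I error is roughly 6–10% in lung and colorectal and about 0–3% in breast. It nearly vanishes if breast is close to 40%. The gate removes the inflation when nothing changes anywhere. The omnibus time and interaction tests stay near 5% with equal groups; unequal dropout was not examined. Breast prevalence, stage distributions and within-person correlation are assumptions. The plan should be changed, but the primary result is not at risk.

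**What to change.** - Take cachexia out of the MANOVA and the mixed ANOVA.
- Analyse the diagnosis with a logistic GEE or mixed logistic model with group, visit and group × visit, over the visits at which it is assessed. State which visits those are. Use a penalised or small-sample version if cells are sparse.
- Analyse the 0–4 stage with a repeated-measures ordinal model over Visits 2 and 3 only.
- Report n (%) with 95% confidence intervals and absolute risk differences, in place of mean ± SD or median ± range.

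Cost: analysis wording and standard software. No new data, visits or patients are needed.
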